### Trial duration

Patient recruitment began in July 2016 and is planned to finish in December 2017. Once recruited, patients are followed up until they are transferred to GUCH. Data collection is expected to be finished by December 2019. After the data set is locked, analysis and dissemination of results will begin.

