### Intervention

#### Transition programme (intervention group)

This study implements a multicomponent intervention, adapted from a brief transition programme developed by Hilderson *et al*.^23^ Adaptation of the programme followed the intervention mapping process.^24^ Intervention mapping is a thorough method used to build comprehensive programmes for health promotion and consists of six consecutive steps: (1) assessment of the needs of the target population; (2) defining programme objectives by specifying performance and change objectives; (3) determining theory-based intervention methods and practical strategies; (4) designing and producing the intervention programme; (5) adoption and implementation of the intervention; and (6) developing and executing a plan for evaluation.^24^ Applying the intervention mapping method in this study ensures that the intervention is well-grounded and includes the necessary components to target the programme objectives. A detailed description of each of the steps will be given in a related article.

The transition programme includes eight key components: (1) a TC; (2) a written person-centred transition plan; (3) provision of information and education about the condition, treatment and health behaviours; (4) availability by telephone and email; (5) information about and contact with the Grown-Up Congenital Heart Disease (GUCH) clinic; (6) guidance of parents; (7) meeting with peers; and (8) the actual transfer to the GUCH clinic.

These components are implemented in five steps: (1) a first patient visit with the TC; (2) a second outpatient visit with the TC; (3) information day for adolescents and their parents; (4) a third outpatient visit with the TC; and (5) actual transfer to the GUCH clinic. The TCs are specialised nurses at the outpatient clinic of paediatric cardiology who have received specific training in performing this intervention.

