#### Usual care (intervention, control and comparison group)

All adolescents who participate in the study receive usual care, irrespective of whether in the intervention, comparison or control group. Usual care includes visits to an outpatient paediatric cardiology clinic where they meet a nurse and a paediatric cardiologist. Disease complexity determines the frequency of the visits. None of the participating centres have a TC as a part of usual care and there is no documentation of transition plans. It is common practice in Sweden that patients are transferred to adult care around the age of 18 years.

Since usual care can vary across clinics and over time, an assessment of transition-related practices will be carried out in all the centres at the beginning of the intervention and at the end of the study. This assessment will comprise three elements: (1) a structured survey called CHAT (Congenital Heart Adolescent and Transition; on file); (2) interviews with healthcare professionals who are involved in the care for adolescents with CHD in the participating centres and (3) observations of the routine during the clinic visits.

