### Follow-up period and data collection

During the 2-year follow-up period, outcome measurements are assessed on three different occasions: T0, baseline when the participants are 16 years old; T1, midterm when the participants are 17 years; and T2, final data collection when the participants have been transferred to adult care and are ∼18.5–19 years old (see figure 1).

Participants from the intervention group will be mailed the set of questionnaires 1 month before the outpatient clinic visit. If the questionnaires have not been received by the time of the visit, they will have the opportunity to complete them while waiting for their appointment. Patients from the control and comparison groups may not have a scheduled outpatient visit. Therefore, data collection in these groups is completely undertaken by post when the participants are 16 (T0), 17 (T1) and 18.5 years old (T2).

To minimise non-response in the comparison and control groups, a modified Dillman procedure will be used.^26^ Two weeks after the documents are sent, non-responders will receive a first personalised reminder in the form of a text message. If after 4 weeks the questionnaires have not been received, a reminder letter and a new set of questionnaires is sent. After 6 weeks, persistent non-responders are contacted by telephone and asked whether they received the questionnaires, if the mailing address is correct, if they want a new set of questionnaires and if they want to continue participating in the study. After 8 weeks, a last reminder is sent to those who agree to participate in the study during the telephone call.

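### T2, the final outcome measurement, is timed differently in the two randomised arms and tied by its wording to transfer; the sentence on end of follow-up also conflicts with it

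*Protocol article*

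**What the plan says.** All references are to the protocol article.

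- **Trial duration:** "Once recruited, patients are followed up until they are transferred to GUCH". The same section expects data collection to finish by December 2019.
- **Follow-up period and data collection, general definition of T2:** "final data collection when the participants have been transferred to adult care and are ∼18.5–19 years old".
- **Same section, comparison and control groups:** "data collection in these groups is completely undertaken by post when the participants are 16 (T0), 17 (T1) and 18.5 years old (T2"). A staged reminder procedure, running to 8 weeks, is described for these two groups.
- **Same section, intervention group:** "Participants from the intervention group will be mailed the set of questionnaires 1 month before the outpatient clinic visit". Questionnaires not returned by then can be completed while waiting for the appointment. No separate age is given for this group.
- **Healthcare usage:** attendance at a GUCH unit is to be assessed after transfer.
- **Transition programme:** the fifth and last implementation step is "actual transfer to the GUCH clinic".
- **Usual care:** "It is common practice in Sweden that patients are transferred to adult care around the age of 18 years".
- **Statistical analyses plan:** the primary analysis follows intention to treat. It is an unadjusted permutation test between the two groups, with a complementary analysis of covariance adjusted for centre and for baseline variables that differ.

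**The concern.** Two statements do not fit together, and one of them affects the randomised comparison.

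The first is the end of follow-up. One section closes follow-up at transfer; two others plan measurements after it.

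The second is the T2 rule. A randomised comparison needs the outcome measured at the same time, and by a rule that does not depend on what happened under treatment. Here one arm has a calendar rule (age 18.5, by post). The other has a rule made of a clinic visit, a completed transfer and an age range. Two biases could follow:

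- **Age at measurement.** Empowerment is measured in adolescents who are still maturing. If one arm is systematically older at T2, part of any difference may be age. Neither analysis, as the article describes it, adjusts for age at assessment.
- **Completion.** Transfer is the last programme step. If T2 is collected less reliably from intervention patients who have not transferred or have no visit booked, that arm's mean rests more on those who completed the programme. An intention-to-treat comparison is meant to avoid this.

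**Working it through.** **1. The plan's own figures.** The target of 5.25 points is 0.5 SD, so SD = 5.25 / 0.5 = 10.5. With two-sided α = 0.05 and 80% power, n per arm = 2 × (1.960 + 0.842)² / 0.5² = 62.8, i.e. 63. Allowing 10% dropout, 63 / 0.9 = 70. Both stated figures reproduce and are not in question.

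**2. End of follow-up.** Trial duration ends follow-up at transfer. T2 and the GUCH-attendance assessment come after transfer. If transfer happens at about 18, the usual practice described, T2 follows it by 18.5 − 18 = 0.5 to 19 − 18 = 1.0 year. The label "During the 2-year follow-up period, outcome measurements are assessed on three different occasions" does not settle the matter. If entry at age 16 means anywhere from 16.0 to just under 17, the interval from entry to T2 runs from about 18.5 − 17 = 1.5 to 19 − 16 = 3.0 years. The Discussion speaks of more than 2 years.

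**3. T2 rule by randomised arm.**

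| | Comparison | Intervention |
|---|---|---|
| Age | 18.5 | about 18.5–19 |
| What prompts mailing | age | one month before a clinic visit |
| Transfer in the wording | only in the general definition | general definition; also the last programme step |
| Reminders described | yes, to 8 weeks | not described; completion at the visit instead |

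The largest difference in target age is 19 − 18.5 = 0.5 year, with the intervention arm later. The three coordinator visits precede transfer in the order of steps, so none of them is obviously the visit that prompts a post-transfer T2. The article does not say which visit does.

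**4. Size of a completion effect (illustration, not an estimate).** Suppose a fraction f of the intervention arm gives no T2 score and would have scored 0.5 SD below those who do, with no matching loss in the comparison arm. The observed arm mean is then too high by f × 0.5 SD:

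- f = 0.10: 0.05 SD = 0.05 × 10.5 = 0.525 points, 10% of the 5.25-point target.
- f = 0.20: 0.10 SD = 0.10 × 10.5 = 1.05 points, 20% of the target.

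With 63 per arm, the standard error of the difference is √(2/63) = 0.178 SD. With no true effect, the chance of p ≤ 0.05 becomes P(Z > 1.96 − 0.05/0.178) + P(Z < −1.96 − 0.05/0.178) = 5.9% for f = 0.10. The same sum gives 8.7% for f = 0.20.

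Precision is a smaller matter. Losing 20% of 70 leaves 56; with 63 in the other arm, power is 77.7%. The dropout allowance protects power but not against selective loss.

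**5. Calendar check for a common age.** A patient recruited at exactly 16.0 at the end of December 2017 is 18.0 at the end of December 2019 and 18.5 in mid-2020. Assuming uniform recruitment from July 2016 to December 2017, the share still under 18.5 at the close is about 8% if entry age is uniform over 16–17, and about 33% if all enter at 16.0.

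**The case against.** The strongest case on the other side has four parts.

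- **The Trial duration sentence is a summary.** A reader might infer that a centre obeying it would stop before T2 and lose the final outcome. The documents do not support that. The data-collection section is the operative schedule and names T2. The article also mentions operating procedures, not shown, that cover survey completion. In addition, age 18 is described as common Swedish practice, not as a trial rule, and a patient transferred at about 18.5 could satisfy both sections. What stands is a wording conflict.
- **An age is given.** A reader might also infer that an intervention patient who never transfers has no prompt for T2 at all. That is too strong: the general definition carries an age beside the transfer condition, and nothing says such patients are dropped. The rule is unclear rather than absent.
- **The bias is assumed.** Nothing in the documents gives a non-transfer rate or a score deficit, and since transfer around 18 is usual for everyone, failing to transfer need not mark failure of the programme. This stands, so the figures in step 4 only show scale. The 6-month age gap is likewise a maximum, and postal reminders would shift some comparison responses later and narrow it.
- **Measuring after transfer is a legitimate choice for a transition programme, and missing data belong in the analysis plan.** Both are fair. Neither explains why the two randomised arms should have different timing rules, and an analysis plan cannot fully repair a difference built into collection.

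**Conclusion.** The point holds as a moderate one. The end-of-follow-up sentence must be reconciled with a T2 placed after transfer. More importantly, the stated timing of T2 differs between the randomised arms: a fixed postal age of 18.5 against a visit-linked mailing with a definition that combines transfer and an age of about 18.5–19. T2 could be up to about 6 months later in the intervention arm, and the rule is unclear for intervention patients without a transfer or a visit.

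The size and direction of any age effect are unknown, because the article gives no rate of change of the score with age. The illustrative completion effect of 0.5–1.05 points rests on three assumptions: 10–20% loss in one arm, a 0.5 SD deficit in those lost, and no corresponding loss in the other arm. The conclusion also assumes that the primary comparison is made at T2, as the hypothesis about a 2-year programme suggests. The documents do not show that T2 will go uncollected or that the result will favour the programme.

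**What to change.** 1. In Trial duration, state that each patient is followed until T2 is completed.
2. In Follow-up period and data collection, define T2 by the same pre-set age and window for every randomised patient, whether or not transferred. Use the existing postal route, with its reminders, whenever an intervention patient has no visit inside the window. Apply the same rule to the non-randomised control group.
3. Record transfer status at T2 as a variable.
4. When the age and window are fixed, check that they fit the December 2019 close for patients recruited late and only just 16.

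This concerns only when data are collected; it does not touch when or how patients transfer. The cost is a few sentences in the protocol and operating procedures and a few extra mailings. The downside is that some T2 measurements would be taken before transfer, which the recorded transfer status lets the analysis describe.

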### Ethical considerations

Before inclusion in the study, the TCs and DCOs will seek written informed consent from the adolescents and their parents after they have received written and oral information about the study. Participants have the right to withdraw at any point throughout the study. The principles established in the Declaration of Helsinki will be followed during the entire duration of the study.^43^

To ensure confidentiality, personal data are coded. Participant and study-related information is stored in locked cabinets and digital documents are password-protected.

### Follow-up on AEs

All AEs must be reported to the principal investigator and project coordinator within a week. In case of a serious AE, the report must be made immediately. Appropriate measures will be undertaken in every AE in order to ensure patient safety.

### Dissemination

The results of this study will be submitted to peer-reviewed journals for publication following the CONSORT statement.^44^ Abstracts for poster or oral presentations will be submitted to international conferences. Authorship is granted to a collaborator from every participating centre and members of the research group fulfilling the criteria of authorship.^45^
^46^ If possible, we will include ‘on behalf of STEPSTONES-CHD’ in the list of authors. After completion of the study, the data set will be available on formal request.

## Discussion

Previous studies have tried to determine the effectiveness of transition programmes. However, owing to several methodological limitations, the true effect of these interventions is still uncertain.^7^ Therefore, we will conduct a study that assesses the effectiveness of a structured, person-centred transition programme to empower adolescents with CHD in the transition to adulthood. Through the implementation of the proposed transition programme, we expect an increase in the level of empowerment. A high level of empowerment can help the adolescent navigate through the adult care system, participate in care planning, and increase self-management and decision-making skills.^8^

The intervention in this trial was designed and initially evaluated by Hilderson *et al*^23^
^42^ in Belgium. Therefore, it was important to determine if the intervention components were suitable in the Swedish setting. To accomplish this, five preparatory studies were carried out (four qualitative, one quantitative study). The qualitative studies included individual and focus group interviews with young persons with CHD and their parents.^47^
^48^ These studies provided an overview of the current transition practices in Sweden and the needs of this population before the transfer to adult care. The quantitative study was a cross-sectional study including 205 young persons with CHD, and served as a pilot-test for our primary outcome measurement. Furthermore, the intervention was discussed with a panel of international experts with experience in transition research in adolescents with chronic conditions and patient representatives.

The preparatory studies and the discussion with the panel of international experts improved the quality, feasibility and acceptability of the intervention. This interdisciplinary and comprehensive approach increases the chance of producing a high-quality intervention with positive results.^49^

This study has several strengths, because we explicitly take limitations of prior studies into account. First, we employ an RCT which is the gold standard for the assessment of the effectiveness of interventions and provides the highest level of evidence. The stratified block randomisation that we undertake ensures that the intervention and comparison groups are balanced and that potential confounding factors, such as complexity of the disease or centre characteristics, are equally distributed and therefore minimise the risk of biasing the results.

Second, the proposed hybrid experimental design allows us to account for potential contamination of the control group. Indeed, the three arms allow performance of direct comparison between the intervention and comparison group while enabling a comparison of findings with those obtained in intervention-naive centres.

Third, patient empowerment is used as the primary outcome. Empowerment is argued to be important for the development and application of skills to promote behavioural changes in the adolescents.^10^ Admittedly, empowerment can be seen both as a process and an outcome.^10^ However, being an intermediate outcome, empowerment can be argued to be proximal to the intervention, whereas continuing cardiac care, reduced morbidity or mortality are probably the ultimate, but more distal outcomes.

Fourth, the PCC approach that is used throughout the transition programme is an important asset in the process of empowering patients.^11^ Providing transitional care from a person-centred perspective is novel and has not been evaluated before in this age group.

Fifth, we follow-up the patients for more than 2 years. While doing so, we substantially expand the follow-up period of 12 months as used in prior studies.^7^

Sixth, since usual care may vary across centres and over time, we carry out a formal usual care assessment. Such a usual care assessment is important to draw firm conclusions, and yet this is seldom performed in clinical trials.^50^

Irrespective of these strengths, we anticipate some limitations as well. First, we are not able to blind the participants or the healthcare team that will perform the intervention. To minimise a potential impact, neither the therapeutic team nor the TCs participate in the data analysis. Second, there is a possibility of a relatively long period of recruitment for participants which can require extending the trial period and delaying data analysis. Third, transition interventions have been advised to start early on, for example, between 10 and 12 years of age, and have a long follow-up.^51^ Furthermore, a long follow-up allows continuity of care to be measured in this population and provides insight into the effects of the transition programme over this parameter. Although we recognise the importance of starting early, it would have jeopardised the feasibility of the study, because it would have taken almost a decade to finish recruitment and follow-up until the age of 18 years. Nonetheless, it could be possible to later on assess loss of follow-up in a separate study.

## Conclusion

This article described the study protocol for a study to assess the effectiveness of a structured, person-centred transition programme for young persons with CHD. This study accounts for limitations of previous research and addresses an existing gap in the evidence of transitional care. It is hoped that the findings will provide strong evidence of the effectiveness of this intervention in young people with CHD. If successful, this transition programme could potentially be implemented as part of routine care provided to young persons with CHD, and transfer to other chronic conditions can be explored.

### Trial status

Status of the trial at the time of submission: patient recruitment.
